### Study interventions

At each hospital, the patient’s tobacco-use history is assessed at bedside by an admitting nurse and recorded in the EMR. A TTS at each hospital reviews the EMR for initial study eligibility (prescreening) prior to conducting a bedside consult and screening visit. All study participants receive a brief (10-minute) bedside tobacco-use evaluation and cessation consult that serves as the usual care condition. All intervention service and medication use, both as an inpatient and after discharge, will be tracked for all study participants. Internal evaluation data indicate the use of outpatient cessation services and medications following hospital discharge was extremely rare (<1% of discharged smokers) among KPNW and OHSU members.

We expect that about 15% of UC recipients will be smoke-free at six months. Unpublished evaluation data for hospitalized KPNW members and OHSU consult recipients suggest about 15% of discharged patients will remain abstinent six months after discharge. Stevens *et al*. (2000) [10] reported a 14.6% quit rate for KPNW hospitalized smokers receiving an intervention similar to our usual care. We estimate that 23% of AR + IVR recipients will be abstinent at six months, given an odds ratio of 1.65, compared to UC recipients [3].

#### *Inpatient tobacco cessation consult (usual care)*

The usual care (UC) intervention provided by the TTS involves a tobacco-use and quit history assessment, discussion of the health consequences of tobacco use and benefits of quitting, and tailored discharge treatment recommendations based on the patient’s tobacco history and personal circumstances. Tobacco-use assessment includes the types of tobacco used, amount used per day, age at initiation, and use by other family members. Quit history includes the number of past quit attempts made, how long ago they last tried to quit, and their experience with using cessation programs and medications. If they used medications, patients are asked about the types of medications used (nicotine replacement therapy [NRT], bupropion, varenicline), how they liked it, and if they experienced any side effects. If appropriate, a tailored discussion is provided of the relationship between tobacco exposure and the patient’s diagnosis, and the health benefits from remaining abstinent. Patients are encouraged to remain abstinent after discharge and provided printed information about available outpatient resources.

UC recipients are provided printed information and a brief overview of existing counseling programs and FDA-approved cessation medications that are typically covered by the patient’s health insurance. UC patients are informed about how to access available services on their own, that is, the TTS does not actively assist the patient in enrolling in a program or ordering medications.

At KPNW, patients access outpatient cessation services and medications through the Health Education Services (HES) department. Patients can enroll in telephone-based and in-person counseling programs, or an interactive web-based program, by contacting HES on their own. Available medications include over-the-counter NRT (transdermal patch, gum, lozenges) and prescription bupropion and varenicline. KPNW patients are charged a small copayment for the services they select, and must enroll in an approved counseling program in order to receive medications at copay. Patients can purchase cessation medications at discharge, typically through the patient’s attending physician; however, the patient will be required to enroll in a counseling program through HES in order to get medications at copay.

At OHSU, patients are provided information about alternative counseling programs and available NRT products (the patch, gum, lozenges, nasal sprays), bupropion, and varenicline that are typically covered by insurance. Patients are encouraged to call their insurance provider to determine cessation program coverage. Patients with Medicare, Medicaid, or no insurance coverage are given information about telephone counseling provided through the state quit line ([name]).

#### *AR + IVR Intervention*

AR + IVR assigned patients are assessed for interest and willingness to enroll in stop-smoking services following discharge. Those who express interest are helped to enroll in available programs before leaving the hospital and staff initiate discharge orders for cessation medications. At KPNW, available programs include alternative telephone counseling programs, individual and group classes, and an interactive web-based program. All programs, except the web-based program, have been shown to be effective at helping smokers quit [9,15,18]. KPNW currently offers nicotine replacement therapy (transdermal patches, lozenges, gum), bupropion, and varenicline. OHSU participants will be offered enrollment in the Oregon Tobacco Quit Line (OTQL) and provided information about available resources and medication options. Information about study enrollment and recommended options for postdischarge cessation treatment will be sent to each patient’s primary source of health care via internal EMR notes or external fax or electronic notes. At both sites, the out-of-pocket costs for enrolled services are determined by participants’ insurance coverage.

#### *IVR follow-up calls*

After discharge, AR + IVR recipients receive four IVR follow-up calls, at days 4, 14, 28, and 49 using Eliza Corporation’s IVR system [19]. The call receipt window will be +4 days for the initial call, and ±4 days for each subsequent call. Participants are prompted for information on current smoking status, cessation program enrollment status, and assessment of cessation medication use. Patients also receive brief, tailored, supportive messages to help them stay off cigarettes. These messages include encouragement to enroll in cessation programs, use cessation medications, or to speak to their doctor to determine the best course of treatment. IVR alerts are generated when a patient indicates that he/she would like to speak to an OTQL quit coach or KP health coach during the call. Study staff members facilitate a callback from the respective coach.

#### *Intervention fidelity*

All research staff will be trained and certified in good clinical practice. Prior to study implementation, all TTSs are trained in how to deliver tobacco-dependence treatment to hospitalized patients based on the OHSU model. TTSs are also monitored during initial piloting and will participate in ongoing case management discussions. Other staff will receive appropriate training in use of the study’s electronic data management system at each site and in coding rules to complete the forms properly.

We monitor intervention fidelity by tracking inpatient cessation service delivery, assisted referrals to outpatient counseling and medications, notifications to primary care providers, and EMR-documented and self-reported cessation service use at follow-up. Inpatient counseling is tracked by documenting TTS-patient interaction time, and by documenting cessation topics discussed during the consult. A treatment form is used to record TTS-patient discussion of tobacco use and quitting history, past cessation service and medications use, current inpatient NRT dispenses and comfort, risk factors for maintaining abstinence, medical contraindications for medication use after discharge, interest in remaining abstinent after discharge, and outpatient treatment recommendations provided. The intervention protocol and treatment form do not specify that a particular topic order must be followed by the TTS. Instead, the form is completed based on topics discussed. Treatment data are recorded and monitored for completeness and additional training conducted as needed.

For study participants randomized to the AR + IVR condition, we obtain documentation of assisted referral outcome (acceptance/refusal of referral, discharge medication ordered), primary care/usual care provider notification completed, and IVR enrollment. Outpatient intervention use for all enrolled participants is obtained during the study period from EMR records and from patient self-reports at follow-up. The IVR intervention is provided via a standard IVR automated calling system for participants at both sites. The content for each call is standard for both hospitals, with some site-specific tailoring. Each call uses branching logic based on information provided from the previous call to gather more accurate and personalized information.

### Safety monitoring plan

Behavioral counseling and FDA-approved cessation medications are considered low-risk interventions for tobacco-use treatment. Adverse events (AEs) associated with medication use are well known, for example, skin rashes, irritability. In some instances, serious adverse events (SAEs) linked to increased risk of suicide have been documented among bupropion and varenicline users [20-22]. This trial involves patients hospitalized for potentially serious health conditions, which increases the risks of re-hospitalization or death.

This study follows the CHART DSMB recommendations, and KPNW and OHSU IRB policies, for tracking and reporting SAEs and AEs. An adverse event tracking and reporting system is used to monitor expected and unexpected SAEs and AEs reported by participants at six- and twelve-month follow-up. The principal investigator or medical monitor will review reported events to determine if they are study-related. Unexpected or potentially study-related AEs and SAEs, including confidentiality breaches, will be reported to the local IRBs within forty-eight hours of identification, and to the DSMB within seven days. SAEs and AEs that are not study-related will be reported to the DSMB every six months and to the local IRBs every twelve months.

### Study measures

Intervention delivery and data collection occur at an inpatient tobacco-cessation consult and screening/recruitment visit, postdischarge IVR telephone calls (AR + IVR only), in-person follow-up interview at six months postrandomization, and during a telephone interview at twelve months. Procedures are standardized as much as possible between the two settings in order to avoid confounding differences in recruiting methods due to site differences. Furthermore, the primary and secondary outcomes for this study have been harmonized with other CHART studies following recommendations of the CHART DSMB.

#### *Primary outcome*

The primary outcome for the I-TSAR study is self-reported thirty-day abstinence from cigarettes at six months postrandomization for AR + IVR compared to UC. Data on days since the last cigarette (even a puff) are collected from participants at six- and twelve-month follow-up assessments. The number of days since the last cigarette was smoked allows calculation of seven-day, thirty-day, and continuous abstinence as secondary outcomes. Biochemical validation of self-reported abstinence is obtained at six months and reported as an additional outcome. All participants are given an exhaled carbon monoxide assessment at the six-month in-person assessment using a Bedfont Smokerlyzer Carbon Monoxide Monitor (Bedfont Scientific Ltd., Maidstone, Kent, UK) [23]. Self-reported abstinence of ≥7 days is verified by a CO level ≤8 parts per million (ppm). For comparison with other CHART studies, self-reported quitting is confirmed using a salivary cotinine (NicAlert) test strip (Nymox Pharmaceutical Corp., Hasbrouck Heights, NJ, USA). Salivary cotinine measurement of ≤50 ng/ml confirms abstinence [24]. Self-reported quitters using nicotine replacement products at the time of the six-month assessment will be considered as ‘confirmed quitters’ by a CO level of ≤10 ppm.

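### Two CO limits (≤8 ppm, and ≤10 ppm for NRT users) are stated without saying which rule defines biochemically confirmed seven-day abstinence, so classification may depend on post-randomization NRT use

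*Protocol article*

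**What the plan says.** The Primary outcome section gives three biochemical rules in this order.

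- General CO rule: "Self-reported abstinence of ≥7 days is verified by a CO level ≤8 parts per million (ppm").
- Cotinine rule: "For comparison with other CHART studies, self-reported quitting is confirmed using a salivary cotinine (NicAlert) test strip", with the limit "Salivary cotinine measurement of ≤50 ng/ml confirms abstinence".
- NRT rule: a separate limit covers "Self-reported quitters using nicotine replacement products at the time of the six-month assessment". In either arm, these participants count as confirmed "by a CO level of ≤10 ppm".

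The status of these measures is stated: "Biochemical validation of self-reported abstinence is obtained at six months and reported as an additional outcome". The primary outcome is self-reported thirty-day abstinence. The Abstract and the section Covariates and effect modifiers each name a single biochemically confirmed seven-day outcome at six months. Neither says which of the three rules defines it.

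On medication, the AR + IVR Intervention section says that for interested patients "staff initiate discharge orders for cessation medications", and the IVR messages encourage medication use. Under usual care the specialist gives information but no active help with ordering.

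**The concern.** NRT supplies nicotine, not carbon monoxide. NRT use is therefore a good reason to judge a participant on CO in place of cotinine, but it does not explain a higher CO limit. If both CO limits feed one outcome, an NRT user reading 9 or 10 ppm is a confirmed quitter and a non-user with the same reading is not.

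NRT use at six months is determined after randomization, and the arms are designed to differ in help with cessation medication. A definition that loosens with such a factor can add more confirmed quitters to one arm than to the other without any difference in smoking. The confirmed outcome is the biochemical check on a self-reported primary outcome, given by participants who know whether they received a referral and calls. Its definition should be the same for all of them.

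**Working it through.** **1. The plan's own design figure.** The Power section gives 864 participants for 15% v 23%, 2:1 allocation, two-tailed α of 0.05 and 80% power, without continuity correction. With pooled p̄ = (0.15 + 2 × 0.23)/3 = 0.2033:

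n(UC) = [1.96 × √(1.5 × 0.2033 × 0.7967) + 0.8416 × √(0.15 × 0.85 + 0.23 × 0.77/2)]² / 0.08² ≈ 287.9, so 288 UC + 576 AR + IVR = 864.

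This reproduces exactly. It concerns the self-reported outcome and does not depend on any CO rule. It matters here only as the yardstick of 8 percentage points.

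**2. Two readings of the three rules.**

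- Reading A: one CO-based outcome, with ≤8 ppm for most quitters and ≤10 ppm for NRT users. The limit then depends on NRT use.
- Reading B: the trial's own outcome is CO ≤8 ppm for everyone. The CHART comparison is cotinine ≤50 ng/ml, with CO ≤10 ppm in place of cotinine for NRT users. Each definition is then coherent, but an NRT user at 9 or 10 ppm is confirmed under one and not under the other, and the text does not say which one is the reported outcome.

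**3. Size under reading A.** Only self-reported quitters on NRT who read 9 or 10 ppm are affected. Inputs:

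- q, the self-reported quit rate: 15% or 23% (Specific Aim 1), the same in both arms so that the result is bias and not treatment effect.
- n, the share of quitters on NRT at six months: not in the article. Assumed 5% to 30% in AR + IVR and 2% to 5% in UC.
- g, the share of those reading 9 or 10 ppm: not in the article. Assumed 1% to 10%.
- Arm sizes: 600 and 300 (Randomization: 300 and 150 per site, two sites).

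Extra confirmed share in an arm = q × n × g. Tilt with no true effect = q × g × (n_AR − n_UC).

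| q | n_AR | n_UC | g | Tilt (points) | Extra in 600 AR + IVR | Extra in 300 UC |
|---|---|---|---|---|---|---|
| 15% | 5% | 2% | 1% | 0.0045 | 0.045 | 0.009 |
| 15% | 20% | 5% | 5% | 0.11 | 0.90 | 0.11 |
| 15% | 30% | 5% | 10% | 0.375 | 2.70 | 0.23 |
| 23% | 20% | 5% | 5% | 0.17 | 1.38 | 0.17 |
| 23% | 30% | 5% | 10% | 0.575 | 4.14 | 0.35 |
| 23% | 20% | 20% | 10% | 0 | 2.76 | 1.38 |

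More extreme assumed NRT shares, 50% v 10% with g = 10%, give 0.15 × 0.10 × 0.40 = 0.60 points at a common 15%, and 0.23 × 0.10 × 0.40 = 0.92 points at a common 23%.

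**4. Effect on the test.** Assume also that 80% of quitters are confirmed at ≤8 ppm. In the fifth row of the table, p_AR = 0.184 + 0.0069 = 0.1909 and p_UC = 0.184 + 0.00115 = 0.1852. The standard error is √(0.1909 × 0.8091/600 + 0.1852 × 0.8148/300) ≈ 0.0276, so the shift is 0.00575/0.0276 ≈ 0.21 standard errors. The two-sided type I error rises from 5.0% to about 5.5%, the highest value in the table's range.

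**The case against.** The strongest defence is reading B. The ≤10 ppm sentence directly follows the cotinine rule and, like it, speaks of confirming, while the ≤8 ppm rule speaks of verifying. It reads naturally as the substitute for a cotinine test that NRT would contaminate. The Study measures section also says that outcomes were harmonized with the other CHART studies, so the second limit may belong to that comparison. This stands as a plausible reading, and for that reason the ≤10 ppm rule should not simply be deleted. It does not settle which rule defines the reported outcome.

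A reader might go further and infer that the plan tilts the confirmed outcome towards AR + IVR. The article does not support that. The rule applies to NRT users in both arms, and a tilt needs higher NRT use among AR + IVR quitters at six months, for which no figure is given. The last IVR call is at day 49, months before the CO reading. NRT is one option beside bupropion and varenicline, referral may be declined, and OHSU participants are described as receiving information on medication options. The direction is plausible but not shown.

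A reader might also compute the tilt at the design rates of 23% and 15%. With NRT use of 30% to 50% v 10% and g of 5% to 10%, that gives 0.27 to 1.0 points (for example 0.23 × 0.50 × 0.10 − 0.15 × 0.10 × 0.10 = 1.0). This mixes the assumed treatment effect with bias. With equal NRT use of 30% and g = 10% the same formula still returns 0.08 × 0.30 × 0.10 = 0.24 points, although the limit then does not favour either arm. At a common 15% quit rate the same inputs give 0.15 to 0.60 points.

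Finally, CO is not the only objective check, since cotinine is also measured, and the Randomization section says that follow-up staff are blinded to treatment group.

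**Conclusion.** The point holds as a definition that is left open, with a possible bias that depends on how it is read. Two CO limits are stated without a reason, and the article does not say which rule produces the single confirmed seven-day outcome that it lists. Under reading A, classification at 9 or 10 ppm depends on NRT use after randomization. Under reading B, two definitions are left unreconciled.

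Under reading A the tilt with no true effect is about 0 to 0.6 percentage points over the main assumed ranges, against a design difference of 8 points. It stays below 1 point under the more extreme shares and is exactly zero if NRT use among quitters is equal in the arms. These sizes rest on NRT shares and on a 9 to 10 ppm share that are assumed. The primary outcome, its test and the sample size are not affected. The matter is small but worth settling before the confirmed outcome is analysed, because it otherwise leaves a choice of definition open.

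**What to change.** Rewrite the biochemical rules in the Primary outcome section as follows.

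1. The trial's confirmed seven-day abstinence is self-reported abstinence of at least seven days with CO ≤8 ppm, the limit already stated, for every self-reported quitter regardless of NRT use.
2. Cotinine ≤50 ng/ml, with CO ≤10 ppm for NRT users, is kept as a separately labelled CHART-comparison definition.
3. CO ≤10 ppm applied to everyone is reported as a sensitivity analysis.

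A single limit makes the NRT-dependent tilt in the trial's own outcome exactly zero. The cost is a few sentences and no new data, since CO is measured on all participants at the six-month visit. The downsides are that a few NRT users at 9 or 10 ppm become unconfirmed in the trial's own outcome, and that two definitions have to be tabulated.

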#### *Power*

A 2:1 ratio of AR + IVR to UC for 900 randomized participants will provide adequate power to detect an eight percentage point difference in thirty-day point prevalence abstinence at six months (our primary outcome), assuming an unbiased method of assigning an outcome to nonrespondents. The unbalanced design requires 864 participants to achieve 80% power, with two-tailed α set at .05, to detect a difference in thirty-day abstinence of eight percentage points between treatment groups. We expect the UC group will achieve a 15% abstinence rate, based on analyses of EMR data (unpublished) for similar populations at each site. An odds ratio of 1.65 for patients with >30 days of follow-up [3] results in a 23% expected abstinence rate for the AR + IVR group. The power calculations were conservative [25-28] and no continuity correction was applied. Rounding up to 900 total participants added an additional measure of conservatism.

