**Figure 1 F1:**
[figure not shown]
I-TSAR consort diagram.

We will need to recruit about 12% of the estimated 6,250 adult smokers who meet our eligibility criteria in order to meet our recruitment target of 900 smokers over 15 months. Our experience with patient populations suggests that 50% or more of identified smokers will meet the study criteria and be interested in trying to quit [10], and 50% or more of these patients will be interested in participating in the study [3,9,10,15]. Thus, if we underachieve our recruitment goal by half we will still meet our recruitment target.

We expect a high follow-up rate for six- and twelve-month assessments. Studies of KPNW and OHSU patients typically achieve follow-up rates of 85% and above for clinical studies [10,15-17]. Each site employs experienced recruitment staff who use electronic tracking systems that collect and maintain up-to-date scheduling and contact information, notification of upcoming follow-up encounters, and web- and phone-based queries for missing addresses.

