#### *Specific Aim 1: estimate self-reported thirty-day abstinence at six and twelve months for patients assigned to receive inpatient AR + IVR compared to usual care*

Based on KPNW and OHSU member data and meta-analyses of effectiveness of hospital cessation programs with ≥1 month postdischarge follow-up, we expect about 15% of usual care patients and 23% of AR + IVR participants will be abstinent six months following discharge. The primary analysis assumes that nonrespondents are smokers.

The treatment effect on the primary outcome (and other binary outcomes) will be evaluated using logistic regression, logit[Y_ik_] = β_0_ + β_1_X_k_ + e _ik_ (Model 1), where Y_ik_ is the binary indicator of the observed binary smoking status for the i^th^ patient (i = 1,. . .,n_k_) within the k^th^ treatment condition (k = 1,2), X_k_ is the fixed effect of the k^th^ condition, that is, intervention or control, and β_0_, β_1_ are parameters to be estimated. Any difference between the predicted and observed values is left to the residual error (e _ik_) in this model. Multiple regression methods available in SAS PROC Logistic [33] will be used to estimate the parameters of this generalized linear model. The intervention fixed effect will be tested using the score *χ*^2^ test.

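### The power statement assumes a nonresponse rule that the primary analysis does not use and rounds up its own odds ratio, so 900 patients give conditional power from about 69% to 82%

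*Protocol article*

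**What the plan says.** The Power section of the protocol article sets the size of the trial. It opens with "A 2:1 ratio of AR + IVR to UC for 900 randomized participants" and says that this gives adequate power for an eight-point difference, "assuming an unbiased method of assigning an outcome to nonrespondents". It then states: "The unbalanced design requires 864 participants to achieve 80% power", "with two-tailed α set at .05". The usual-care rate is put at 15%. For the intervention arm: "An odds ratio of 1.65 for patients with >30 days of follow-up [3] results in a 23% expected abstinence rate". It adds: "The power calculations were conservative [25-28] and no continuity correction was applied", and describes the rounding up to 900 as a further margin. It makes no separate allowance for loss or death.

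The Data analysis section, under Specific Aim 1, repeats the 15% and 23% and then says: "The primary analysis assumes that nonrespondents are smokers". The test is the score chi-square from logistic regression. The section on missing and incomplete data confirms the smoker rule for the primary hypothesis test and excludes patients who die before follow-up. It also warns that deaths may be more frequent than in other cessation trials. Multiple imputation is mentioned there as something that may be presented, depending on the follow-up achieved.

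Under Recruitment, studies at the two sites are said to "typically achieve follow-up rates of 85% and above for clinical studies".

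**The concern.** The condition attached to the power claim is not the rule that the primary analysis applies. Counting nonrespondents as smokers is an unbiased assignment only if they do all smoke, and the article does not claim that. The missing-data section says only what follows if smokers are more likely to be lost. If some nonrespondents are abstinent, the rule pulls both arms' rates down and narrows the difference under test.

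Separately, the eight-point target is presented as the result of an odds ratio of 1.65, but that odds ratio gives slightly less than eight points. The shortfall looks trivial as a rate but costs several points of power.

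At stake is how the primary result is read. A null result would be judged against a stated power that holds only under particular conditions, and the article does not say whether those conditions are met.

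**Working it through.** **Inputs.** Two-sided alpha 0.05, 300 usual care (p1) and 600 AR + IVR (p2), 15% v 23%, odds ratio 1.65, no continuity correction (Power section); follow-up of 85% or more (Recruitment); nonrespondent counted as smoker and deaths excluded (Specific Aim 1; Missing and incomplete data). The number of deaths is not given, so 5% is used as an assumption.

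**1. The plan's own figure.** Pooled-variance formula at 2:1, with p̄ = (p1 + 2·p2)/3 = (0.15 + 0.46)/3 = 0.2033:

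n(UC) = [1.960·√(1.5·p̄(1−p̄)) + 0.842·√(p1(1−p1) + p2(1−p2)/2)]² / (p2 − p1)² = 287.9, rounded up to 288; 3 × 288 = 864.

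This reproduces the stated total exactly.

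Power = Φ[(p2 − p1 − 1.960·SE0)/SE1], where SE0 uses the pooled rate and SE1 the separate rates. At 300/600, SE0 = 0.02846 and SE1 = 0.02684, so (0.08 − 0.05578)/0.02684 = 0.903 and power is 81.7%. At 288/576 it is 80.0%.

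**2. The odds ratio.** Odds at 15% are 0.15/0.85 = 0.1765; times 1.65 is 0.2912; 0.2912/1.2912 = 22.55%. The difference is 7.55 points. Conversely, (0.23/0.77)/(0.15/0.85) = 1.69. With 15% v 22.55% and complete follow-up, 900 gives 77.3%, and 80% needs 963.

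**3. Nonrespondents as smokers.** Assume that 15% and the intervention rate are true rates in everyone randomized, and that nonrespondents quit as often as respondents in both arms. With follow-up proportion f, the analysed rates are f·p1 and f·p2, and all 900 stay in the denominator.

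| Follow-up | Difference, 23% | Power, 23% | Difference, 22.55% | Power, 22.55% |
|---|---|---|---|---|
| 100% | 8.0 | 81.7% | 7.55 | 77.3% |
| 95% | 7.6 | 79.1% | 7.2 | 74.6% |
| 90% | 7.2 | 76.3% | 6.8 | 71.6% |
| 85% | 6.8 | 73.2% | 6.4 | 68.5% |

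At 85% the analysed rates are 12.75% v 19.55% with 23%, or 12.75% v 19.17% with 22.55%. The totals needed for 80% would be 1,056 and 1,173.

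**4. Other behaviour of nonrespondents, at 85% follow-up.** If they quit half as often as respondents, the respondents' rate is p/(0.85 + 0.5 × 0.15) = p/0.925, and the analysed rate is 0.85p/0.925. That is 13.8% v 21.1%, with power 77.4%. If none of them quit, the smoker rule is unbiased and nothing shrinks: 81.7% with 23%, 77.3% with 22.55%. The same two figures hold if 15% and 23% already count nonrespondents as smokers.

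**5. Deaths.** These do reduce the number analysed. The margin is 900 − 864 = 36 patients, or 4%. With an assumed 5% excluded (285/570) and no other loss, power is 79.6% with 23% and 75.1% with 22.55%.

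**The case against.** The strongest reply is that nothing was miscalculated. The 864 is exact for the eight-point difference that the article names as its target, and 900 exceeds 80% for it. Specific Aim 1 gives the 15% and 23% in the same paragraph as the smoker rule, so they can be read as the rates expected under that rule. Even if they are not, the missing-data section contemplates smokers being lost more often, which would lessen the shrinkage. The 85% is the floor of the expected follow-up, not its centre. The 23% is a rounded estimate, and its implied odds ratio of 1.69 lies well within the interval of 1.44 to 1.90 quoted in the Discussion.

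Most of this stands, and it rules out some stronger readings:

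- A reader might infer that the trial simply has 69% power. The documents do not support that as a fact. It needs the rates to be free of the smoker rule, nonrespondents to quit as often as respondents, follow-up at its floor, and the unrounded rate, all together.
- A reader might pair the 6.8-point difference at 85% follow-up with 69%. It goes with 73.2%; the 68.5% goes with 6.4 points.
- A reader might say that a continuity correction, which raises the total to 921, shows the trial to be too small. With one binary predictor, the planned score test is the uncorrected chi-square, so the uncorrected formula is the matching one.
- A reader might treat the 36-patient margin as cover for loss to follow-up. Under the smoker rule lost patients stay in the denominator; only deaths use up the margin.

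The reply leaves two things unanswered. The Power section names an unbiased assignment, not the smoker rule, and no section says how the planning rates treat nonrespondents. And the effect of the rounding on power needs no missing-data assumption at all.

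**Conclusion.** The point holds as a mismatch in the power statement, not as a calculation error. At the protocol's own odds ratio, 900 patients give 77.3%, short of 80% even with everyone followed up. Under the actual primary rule, power before deaths lies between 73.2% and 81.7% with 23%, and between 68.5% and 77.3% with 22.55%. This holds for follow-up of 85% or more, nonresponse equal in the two arms, and nonrespondents quitting no more often than respondents. Where in the range the trial sits depends on what the 15% and 23% mean and on how nonrespondents behave, and the article settles neither. Deaths lower the figures further by an amount that the article does not give. Omitting the continuity correction is consistent with the planned test, but it makes the required number smaller, so it is no ground for calling the calculation conservative.

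**What to change.** In the Power section:

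- State whether the 15% and 23% already count nonrespondents as smokers.
- Replace the condition about unbiased assignment with the rule that the primary analysis uses.
- Restate power at 900 as a conditional range: 81.7% for 15% v 23% if the rates already include the rule or nonrespondents do not quit, falling to 79.1%, 76.3% and 73.2% at 95%, 90% and 85% follow-up if they quit as often as respondents. Note that excluded deaths lower these figures.
- Make the effect size consistent: either use 22.6% and 7.6 points, with the corresponding range of 77.3% down to 68.5%, or keep 23% and state the planned odds ratio as 1.69.
- Do not rest the word conservative on the omitted continuity correction.

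In the section on missing and incomplete data, make the multiple-imputation analysis a fixed sensitivity analysis beside the primary result, rather than one that depends on the follow-up achieved.

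The cost is wording and a less favourable stated power. The primary outcome, the test and the number of patients do not change.
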